## Abstract

**Background:**

Gyejibongnyeong-hwan (GJBNH) is one of the most popular Korean medicine formulas for menstrual pain of dysmenorrhea. The concept of blood stagnation in Korean medicine is considered the main factor of causing abdominal pain, or cramps, during menstrual periods. To treat the symptoms, GJBNH is used to fluidify the stagnated blood and induce the blood flow to be smooth, reducing pain as the result. The purpose of this trial is to identify the efficacy of GJBNH in dysmenorrhea caused by blood stagnation.

**Methods:**

This study is a multi-centre, randomised, double-blind, controlled trial with two parallel arms: the group taking GJBNH and the group taking placebo. 100 patients (women from age 18 to 35) will be enrolled to the trial. Through randomization 50 patients will be in experiment arm, and the other 50 patients will be in control arm. At the second visit (baseline), all participants who were already screened that they fulfil both the inclusion and the exclusion criteria will be randomised into two groups. Each group will take the intervention three times per day during two menstrual cycles. After the treatment for two cycles, each patient will be followed up during their 3^rd^, 4^th ^and 5^th ^menstrual cycles. From the screening (Visit 1) through the second follow-up (Visit 6) the entire process will take 25 weeks.

**Discussion:**

This trial will provide evidence for the effectiveness of GJBNH in treating periodical pain due to dysmenorrhea that is caused by blood stagnation. The primary outcome between the two groups will be measured by changes in the Visual Analogue Score (VAS) of pain. The secondary outcome will be measured by the Blood Stagnation Scale, the Short-form McGill questionnaire and the COX menstrual symptom scale. Analysis of covariance (ANCOVA) and repeated measured ANOVA will be used to analyze the data analysis.

**Trial registration:**

Current Controlled Trials: ISRCTN30426947

## Background

Dysmenorrhea is a very common medical condition in women worldwide. The prevalence varies from 45% to 95% of all women depending on its definition [1]. In Korea, 78.3% of all adolescent girls have dysmenorrhea during their menstrual periods [2]. The most common symptom of dysmenorrhea is abdominal pain, or cramp. It is not only painful but interferes with daily activities, and it has been the leading cause of recurrent short-term school absence [3].

The most prominent physiological cause of dysmenorrhea in allopathic medicine is the production of uterine prostaglandins. Endometrial cells release prostaglandins when they are deciduous. The released prostaglandins stimulate myometrial contractions and cause ischemia. This results in abdominal pain, which has been the source of difficulties that women have to cope with in their daily lives.

But the explanation for the pain is different in Traditional Korean Medicine. In Traditional Korean Medicine, the causes of sicknesses are classified according to symptoms and signs. Traditional Korean Medical specialists diagnose the cause of the sickness by symptoms and signs and prescribe the appropriate remedy.

The most common factor causing dysmenorrhea in Traditional Korean Medicine is blood stagnation in the uterus. 'Flow' is a very important concept in Traditional Korean Medicine. If the flow of *qi *and blood inside the both is smooth, the body is healthy without any diseases. But if the flow is interrupted, it causes pain. This can be applicable to *qi *and blood. Blood stagnation means obstructed blood flow, and a woman experiencing dysmenorrhea can be explained by blood stagnation in her body. The signs of blood stagnation are getting bruised easily, tender abdominal pain, etc.

The first treatment of dysmenorrhea in allopathic medicine is an over-the-counter drug, especially non-steroidal anti-inflammatory drugs (NSAIDs) such as Ibuprofen, Naproxen, Mefenamic, etc. [3,4]. These drugs, however, have failed to show effect in 20% to 25% of women, and moreover some women complain about digestive disorders while taking the drug. In this case, Korean herbal medicine can be a plausible alternative [5].

Gyejibongnyeong-hwan (GJBNH) is one of the most popular Korean medicine formulas for periodical pain due to dysmenorrhea. GJBNH fluidifies blood to induce smooth blood flow and reduce pain [6]. However, the evidence of the effect of GJBNH in treating dysmenorrea has been reported mostly in the form of case reports. In the era of evidence medicine, high quality evidence is mandatory for a medical formula to be proven effective.

The purpose of this trial is to identify the efficacy of GJBNH in dysmenorrhea caused by blood stagnation.

## Methods

### Objectives & Hypothesis

#### Objectives

1) Clinically significant improvement in the severity of pain caused by dysmenorrhea

2) Correlation between blood stagnation level and pain severity

#### Hypothesis

The hypothesis is that GJBNH will reduce menstrual pain more effectively than placebo after taking the intervention--GJBNH or the placebo--for two menstrual cycles.

### Setting

This trial is a randomized, double-blind, parallel group, placebo-controlled phase IV trial. There are three investigational sites: Oriental Medicine Obstetrics and Gynecology Clinic of Kyung Hee Medical Center in Seoul, Obstetrics and Gynecology Clinic of Won Kwang Oriental Hospital in Gunpo, and Obstetrics and Gynecology Clinic of Kyung Won Gil Oriental Medical Hospital of Kyung Won University in Incheon, Korea. Participants will be treated as outpatients in these sites. Before the beginning of the trial, the protocol of the trial has been approved by the Institutional Review Board (IRB). All participants will take GJBNH or placebo for two menstrual cycles (about eight weeks). They will be followed up during three menstrual cycles. It takes five menstrual cycles (about 20 weeks) from baseline to finish. The total span from screening (visit 1) to finish (2^nd ^follow-up) can vary according to the participant's period. Figure 1 is an overview of this trial.

**Figure 1 F1:**
[figure not shown]
**Study flow chart**.

### Participants

#### Inclusion Criteria

The inclusion criteria are as follow (Table 1).

**Table 1 T1:** Inclusion criteria of GJBNH study

**Inclusion criteria**

1. Female aged 18 to 35 years.
2. Women whose period cycle was 30 ± 3 days during last 3 months.
3. Women who have menstrual pain (dysmenorrhea) over 6 degrees by the Visual Analogue Scale (VAS) at screening.
4. Women who are diagnosed with blood stagnation by two oriental medical gynecologic specialists.
5. Have given a written informed consent form
6. Have given a written informed consent form for genetic study.

#### Exclusion Criteria

The exclusion criteria of this trial are described in Table 2.

**Table 2 T2:** Exclusion criteria of GJBNH study

**Exclusion criteria**

1. A woman who has major neuro-psychiatric disorder (schizophrenia, epilepsy, alcohol abuse, anorexia, etc.) or has history of major neuro-psychiatric disorder.
2. A woman who is planning to have a baby.
3. A woman who is taking anti-depressant, anti-serotonin, barbiturate, or psychotropic drugs.

### Interventions

Gyejibongnyeong-hwan (GJBNH) is a Traditional Korean Medicine formula. It consists of *Cinnamomi ramulus, Poria, Moutan cortex, Persicae semen*, and *Paeoniae radix*. Gyejibongnyeong-hwan is a small brown ball-like tablet. A single dose of GJBNH is one pouch in which there are 20~30 tablets. The placebo medicine is made of lactose, corn starch and food coloring and has a similar appearance, shape, weight, taste, and color as GJBNH. The treatment drug and placebo will be provided by Hanpoong Pharm & Foods Co., Ltd.

### Rescue medication

Ten pain killer pills will be given during each treatment cycle as rescue medication. If the participant can not endure the pain, she can take the rescue medication. But all participants should not take any pain-killer except given by the investigator. If the participant takes any other drug than what is given from the trial, it should be described in the case-report form (CRF). Any participant taking drugs that can influence the outcome such as NSAIDs or oral contraceptive pills will be excluded from the trial.

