### Outcomes

#### Primary outcome

The primary outcome in this study is the change in the Visual Analogue Scale (VAS) of average menstrual pain between the baseline (Visit 2) and after the treatment (Visit 4). A 100 mm VAS will be used to assess average level of pain during the menstrual period.

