#### Secondary outcome

The secondary outcome measures include the VAS (the maximum pain during the menstrual period), the Blood Stagnation Scale, the Short Form McGill Pain Questionnaire [7], and the Cox Menstrual Symptom Scale [8]. The quantity of pain killer pills taken during the menstrual period would be recorded at every visit. Heart Rate Variability (HRV) will also be measured.

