### Sample size

The primary outcome in this trial is the change of the Visual Analogue Score (VAS) of average pain in the menstrual period between the baseline (Visit 2) and after treatment (Visit 4). The hypothesis is

H0:δ=Δ1-Δ2=0

H1:δ=Δ1-Δ2≠0

Δ1: The change of VAS score between Visit 4 and baseline in GJBNH group

Δ2: The change of VAS score between Visit 4 and baseline in placebo control

As a reference, we have chosen the study of Choi et. al. [6] and Yeh LL [9]. The mean (± standard deviation, SD) change of the VAS in GJBNH group (n = 13) was 2.42 (± 2.04) and those in placebo control group (n = 38) was 1.08 (± 2.14). We used the mean difference between groups, 1.34 (= 2.42-1.08), as a clinically significant improvement worth to detect and 2.12 as its pooled standard deviation. With 5% of two-sided significance level and 80% of statistical power, we needed to randomly assign fifty participants in each group considering approximately 20% of drop-out rate.

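### Removing randomised women who take an outside analgesic or other outcome-influencing drug leaves a collectable Visit 4 VAS to imputation in the ITT analysis

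*Protocol article*

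**What the plan says.** All points are in the protocol article.

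- **Rescue medication.** The supply is fixed: "Ten pain killer pills will be given during each treatment cycle as rescue medication". Whether to use it is left to the woman: "If the participant can not endure the pain, she can take the rescue medication". Other pain killers are not allowed, and any non-trial drug is to be written in the case-report form. The section closes with: "Any participant taking drugs that can influence the outcome such as NSAIDs or oral contraceptive pills will be excluded from the trial".
- **Exclusion criteria (Table 2).** The only drug-related item is "A woman who is taking anti-depressant, anti-serotonin, barbiturate, or psychotropic drugs". NSAIDs and oral contraceptives are not listed.
- **Randomization.** Allocation takes place at Visit 2, before the treatment cycles.
- **Primary outcome.** Change in average-pain VAS from Visit 2 to Visit 4.
- **Secondary outcome.** "The quantity of pain killer pills taken during the menstrual period would be recorded at every visit".
- **Statistical method.** ITT is every randomised participant, with multiple imputation of missing data. Per-protocol is completers without deviations.
- **Sample size.** "we needed to randomly assign fifty participants in each group considering approximately 20% of drop-out rate".

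**The concern.** The rule removes a randomised woman because of something she does after randomisation. For NSAIDs the likely trigger is menstrual pain that neither the study treatment nor the supplied pills control, and menstrual pain is the primary outcome. Oral contraceptive use need not be linked to pain.

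The rule is also uneven. A woman who cannot bear the pain and takes the supplied pills stays in, and her VAS counts with an analgesic on board. A woman who takes a different analgesic is removed. Removal is not needed to document the drug, since the case-report form and the pill counts already do that.

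Part of the primary ITT comparison would then rest on a missing-data assumption that cannot be tested, for women whose score was obtainable. A later analysis plan cannot restore a score that was never collected.

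**Working it through.** **1. When the rule acts.** It stands under Rescue medication, directly after a sentence on recording drugs taken during the trial, and it speaks of participants. Its two example drugs are absent from Table 2. Together these point to removal after randomisation.

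**2. What happens to the score.** A woman removed before Visit 4 still belongs to the ITT set. Nothing in the article provides for collecting her Visit 4 VAS, so it becomes a missing value and is imputed.

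**3. The plan's own figure.** Inputs from Sample size: mean changes 2.42 and 1.08 (difference 1.34), SD 2.12, two-sided 5%, power 80%.

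- Pooled SD: √[(12 × 2.04² + 37 × 2.14²)/49] = 2.116, which agrees with 2.12.
- n per arm = 2 × (1.960 + 0.842)² × (2.12/1.34)² = 39.3, so 40; 40/0.80 = 50. The stated 50 per arm is reproduced.
- Standard error of the difference with 50 per arm: 2.12 × √(2/50) = 0.424.

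**4. How removal shifts the estimate.** Let p be the removed share in an arm (T = GJBNH, C = placebo) and g the mean imputed minus mean actual improvement of the removed women. The error in the GJBNH-minus-placebo difference is pT·gT − pC·gC.

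- pT = 5%, pC = 15%, g = +1 in both arms: 0.05 − 0.15 = −0.10. With g = −1: +0.10.
- p = 10% in both arms and equal g: 0.
- p = 10% in both arms, gT = +1, gC = −1: +0.20. With signs reversed: −0.20.

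The article fixes neither p nor g, so it fixes neither sign nor size.

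**5. Simulation over an assumed range** (400,000 women per arm). The mean changes and SD are the plan's, read as 0-10 VAS points. Everything else is assumed:

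- Baseline SD 1.5, 1.8 or 2.0; baseline-to-Visit 4 correlation 0.3 or 0.5.
- Interim VAS with half the mean change, an SD midway between the baseline and Visit 4 SDs, correlation 0.5 with baseline and 0.6 with Visit 4.
- Logistic removal with odds ratio 1.5 or 2 per point, calibrated to 5%, 10%, 15% or 20% of placebo women. This gives 2-13% in GJBNH if removal is driven by Visit 4 pain, and 3-16% if driven by interim pain.
- Imputation by within-arm regression among retained women, the large-sample equivalent of multiple imputation under missing at random.
- Full-follow-up difference = 1.34 − (pC − pT) × relief, where relief is the points by which the other drug lowers the Visit 4 VAS.

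Imputed minus full-follow-up difference, with removal driven by unrecorded Visit 4 pain and imputation from baseline only:

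| Relief (points) | 5% removed | 10% removed | 20% removed |
|---|---|---|---|
| 0 | −0.07 to −0.02 | −0.12 to −0.03 | −0.19 to −0.06 |
| 1 | −0.04 to 0.00 | −0.07 to +0.01 | −0.10 to +0.01 |
| 2 | −0.01 to +0.02 | −0.02 to +0.05 | −0.02 to +0.08 |
| 3 | +0.01 to +0.05 | +0.03 to +0.09 | +0.07 to +0.18 |

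Check of one cell (20%, no relief): the imputed difference is 1.151 to 1.284; minus 1.34 gives −0.19 to −0.06.

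- With an interim VAS added to the imputation model, at 20%: −0.16 to −0.04, −0.07 to +0.03, +0.02 to +0.11 and +0.10 to +0.21 for 0, 1, 2 and 3 points of relief.
- If removal is driven by a recorded interim VAS that is in the model, imputation recovers the difference without the other drug to within 0.004 of 1.34. With 1-3 points of relief that is above the full-follow-up difference by 0.01-0.05 at 5% and 0.03-0.16 at 20%.

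The overall range is −0.19 to +0.21. A repeat run of the main setting moved its limits by about 0.01.

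**6. Effect of keeping the scores.** At 20% use the full-follow-up difference is 1.24-1.27, 1.14-1.21 or 1.04-1.14 for 1, 2 or 3 points of relief. Normal-approximation power with all 50 per arm observed:

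- At 1.24: 1.24/0.424 = 2.92, power about 83%.
- At 1.04: 1.04/0.424 = 2.45, power about 69%.
- With the effect unchanged at 1.34: 88.5%, against 80.7% with 40 observed per arm.

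**The case against.** - **The loss of data is inferred.** The article never says that the Visit 4 VAS is not collected after exclusion, and a condensed article may leave that to the full protocol. This stands as a caveat. But the article states a removal rule, and leaving the trial ordinarily ends data collection.
- **It may be an entry rule.** The Safety assessment section uses a different word, withdrawal, for removal during treatment, and oral contraceptives are a natural eligibility item. This reading is possible, but placement and sequence weigh against it. If it was intended, the sentence is in the wrong section and still needs correcting.
- **Multiple imputation and the drop-out allowance cover it.** Imputation does so only if removal depends on data in the imputation model, and it then estimates the difference without the other drug. The allowance covers lost numbers, not bias.
- **The difference without prohibited analgesics is a legitimate target.** True, and a single standard rescue drug is a common design. Still, the plan commits to ITT on all randomised women and already has a per-protocol set for the deviation-free comparison. Collecting the score closes off neither.
- **The error is small.** The extremes are about half a standard error (0.21/0.424 = 0.50) and need 20% use, which the ten pills per cycle should keep from happening. At 5% the tabulated error is at most about one sixth of a standard error (0.07/0.424 = 0.17). This stands and limits the weight of the point.
- **Keeping the scores can cost more than it saves.** In the extreme case the difference falls by 0.30 (1.34 to 1.04), more than any imputation error found. This also stands, but that fall is what full follow-up would actually show, not an error in estimating it.

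**Conclusion.** The concern holds, as a cheap improvement rather than a serious flaw. On its plain reading the rule creates missing primary-endpoint data in randomised women, for a reason plausibly tied to the outcome, where the data could be collected at a scheduled visit. Relative to full follow-up, the imputed difference may be off by −0.19 to +0.21 VAS points against a planned 1.34. Those limits come from the upper-bound assumption of 20% use in placebo and from assumed relief, correlations and removal mechanisms, none of which the article gives. Neither direction can be claimed. Confidence is moderate, because the full protocol may already keep the Visit 4 score.

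**What to change.** In Rescue medication, replace the closing rule on removal with wording such as:

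> *If a participant takes a drug that may affect the outcome, the drug is recorded in the CRF, she remains in follow-up and her VAS is collected at Visit 4. Observed values are used in the ITT analysis; she is left out of the per-protocol set only.*

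The cost is one sentence. The sample size stays at 50 per arm, with no new visit or procedure. The price is that some ITT scores will be measured under other analgesics and the difference may narrow; the per-protocol analysis shows the result without these women. If the full protocol already keeps the Visit 4 VAS, the sentence only makes that explicit. If an entry restriction was meant, move it to the exclusion criteria.

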### Outcomes

#### Primary outcome

The primary outcome in this study is the change in the Visual Analogue Scale (VAS) of average menstrual pain between the baseline (Visit 2) and after the treatment (Visit 4). A 100 mm VAS will be used to assess average level of pain during the menstrual period.

#### Secondary outcome

The secondary outcome measures include the VAS (the maximum pain during the menstrual period), the Blood Stagnation Scale, the Short Form McGill Pain Questionnaire [7], and the Cox Menstrual Symptom Scale [8]. The quantity of pain killer pills taken during the menstrual period would be recorded at every visit. Heart Rate Variability (HRV) will also be measured.

### Safety assessment

All participants will report any adverse event she had while taking the intervention at every visit. Every adverse event will be described in the CRF. If the adverse event is severe and associates with the trial, the participant will be withdrawn from the trial and appropriate treatment will be given to her. For safety assessment, a liver function test, blood cell count test, physical examination, and urine analysis will be carried out at Visit 4.

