### Statistical method

Efficacy analysis will be performed for both ITT (intention-to treat, all randomly assigned participants) and PP (per-protocol, participants completed the trial without any protocol deviations) data sets. To compare the differences of the average changes of the VAS between the experimental arm and the control arm, the Short Form McGill Pain Questionnaire score, the blood stagnation score, the Cox menstrual score from the baseline (Visit 2) to after the treatment (Visit 4) between two groups, and analysis of covariance (ANCOVA) using the baseline score as a covariate will be used.

For the variables which measure the autonomic nerve system (HF, high frequency; LF, low frequency; HF/LF ratio), similar methods described above or their corresponding non-parametric analysis will be performed as appropriate.

For ITT analysis, missing data will be imputed by MI (Multiple Imputation) method using SAS/MI procedure.

The safety data set will include the participants who take the intervention at least once. For safety analysis, physical examination and self-reported adverse event will be compared by the chi-square test. In addition, the results of liver function tests, blood cell count and urine analysis will be analyzed using the same methods as described in efficacy analysis after classifying these results into normal or abnormal according to their respective normal ranges. The chi-square test will be used to compare the differences between the groups.

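### Women with a severe trial-related adverse event leave the trial, not just the intervention, so their Visit 4 tests and outcomes can go missing because of suspected harm

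*Protocol article*

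**What the plan says.** The protocol article's Safety assessment section sets the rule: "If the adverse event is severe and associates with the trial, the participant will be withdrawn from the trial". It adds that she will receive suitable treatment. The same section states that "a liver function test, blood cell count test, physical examination, and urine analysis will be carried out at Visit 4", and the article gives no other time for these tests.

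The Primary outcome section defines the endpoint as the change in average menstrual pain from Visit 2 to Visit 4. Follow-up goes on after that. The Setting section says "They will be followed up during three menstrual cycles", and the abstract says "From the screening (Visit 1) through the second follow-up (Visit 6) the entire process will take 25 weeks".

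The Statistical method section defines intention-to-treat (ITT) as all randomised women. For safety, "The safety data set will include the participants who take the intervention at least once". On missing data: "For ITT analysis, missing data will be imputed by MI (Multiple Imputation) method using SAS/MI procedure". It also says that "physical examination and self-reported adverse event will be compared by the chi-square test", and that laboratory and urine results are classed as normal or abnormal and compared between arms in the same way.

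**The concern.** The conduct rule and the analysis sets pull in different directions. The Statistical method section keeps every dosed woman in the safety set and every randomised woman in the ITT set. The Safety assessment rule ends participation for the women in whom harm is suspected, at whatever point that happens. If this is before Visit 4, the data those sets need are not collected, although the visits are already planned.

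Two things are at stake:

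- **Safety tests.** The abnormal-result rates can lean towards women who tolerated the treatment.
- **Pain outcome.** Multiple imputation, as usually run, assumes that data are missing at random given what was observed. Here the loss is triggered by an event attributed to the trial, so that assumption is least secure for these women.

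**Working it through.** **The stated sample size.** Inputs from the Sample size section: difference 1.34, SD 2.12, two-sided 5% level, 80% power, about 20% drop-out.

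- Pooled SD: √[(12 × 2.04² + 37 × 2.14²)/49] = 2.116, which rounds to 2.12.
- Needed per arm: 2 × (1.960 + 0.842)² × (2.12/1.34)² = 39.3, so 40.
- With drop-out: 40/0.80 = 50.

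The planned 50 per arm reproduces. Power is 0.807 with 40 observed per arm and 0.885 with 50.

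**What the rule removes.** For a woman withdrawn before Visit 4:

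| Item | Where fixed | After withdrawal from the trial |
|---|---|---|
| The adverse event | Safety assessment | Recorded and compared between arms |
| Laboratory, urine and physical examination tests | Visit 4 | Can be missing |
| Primary pain score | Visit 4 | Can be missing; imputed for ITT |
| Follow-up outcomes | Through Visit 6 | Can be missing |

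**Effect on the primary outcome.** The article gives no rate of severe related events, so two inputs are assumed: a rate p before Visit 4 of 1%, 2% or 4%, and an average gap of 1 SD (2.12) between these women's true and imputed changes. The expected number affected is 50p, and the shift in the arm mean is p × 2.12.

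| Assumed p | Women affected of 50 | Shift in arm mean | Share of 1.34 |
|---|---|---|---|
| 1% | 0.5 | 0.021 | 1.6% |
| 2% | 1.0 | 0.042 | 3.2% |
| 4% | 2.0 | 0.085 | 6.3% |

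The between-arm difference moves by this amount if only one arm is affected. With only these women missing, 48 or more per arm are observed on average, against 40 needed.

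A harsher case leaves the women out of the GJBNH arm altogether and takes a rate f and a gap of d VAS units, so the shift is f × d. With f = 2% and d = 1 it is 0.02 (1.5% of 1.34). With f = 10% and d = 3 it is 0.30 (22%).

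**Effect on the safety tests.** Suppose the affected women are the only ones in an arm with abnormal results, and only observed results are counted. One such woman turns 1/50 into 0/49; two turn 2/50 into 0/48. With all results present, the uncorrected chi-square test gives:

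- 1/50 against 0/50: p = 0.315 (Fisher 1.00)
- 2/50 against 0/50: p = 0.153 (Fisher 0.495)

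The test is non-significant either way. What is lost is the abnormal result itself. If the affected women had normal tests, the rates barely change.

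**The case against.** The strongest reply is that the article condenses a fuller protocol and does not say that assessments stop. Exit tests or contact after withdrawal may be described elsewhere, and withdrawal may loosely mean stopping treatment. This stands in part: the data can go missing, and the article does not show that they must. But the rule is stated, and sites follow its words. An exit test, if there is one, would supply laboratory results but not the Visit 4 pain score or the follow-up outcomes.

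The second reply is that little is lost. The event must be severe, related and before Visit 4 to affect the tests or the primary outcome, and the Discussion describes adverse events as rare. The event is counted, ITT uses imputation, and 20% drop-out is allowed for. The efficacy comparisons described run from Visit 2 to Visit 4, so lost follow-up carries less weight. All of this limits the size. It does not remove the point: a drop-out allowance protects power, and imputation does not replace an observation lost because of harm. The 22% case above needs 10% severe related events and omission of the women instead of the planned imputation, so it should not be read as likely.

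Third, the 0/49 and 0/48 examples assume that only observed tests are counted. The Statistical method section refers laboratory results back to the efficacy methods, which may include imputation. That is a fair reservation, but an imputed normal or abnormal class is still not the woman's own result.

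Finally, the Rescue medication section also excludes women who take certain drugs, and that may be the more frequent loss in a pain trial. It is a separate rule, which this change does not address.

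**Conclusion.** The concern holds as a minor point. Followed as written, the rule gives up data from already scheduled visits for women with suspected harm, while the analysis sets keep those women in. At assumed rates of 1% to 4% and an assumed 1 SD gap, the primary estimate moves by at most 6.3% of the planned difference, and neither power nor the chi-square conclusions are threatened. The practical loss is one or two laboratory, urine or examination results per arm, from the women in whom they would tell most. The size rests entirely on assumed event rates and gaps; the direct reading of the rule does not.

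**What to change.** In Safety assessment, replace withdrawal from the trial with wording such as: *the intervention will be stopped and, with her consent, she continues the scheduled visits, including the Visit 4 tests, through Visit 6*. Keep the commitment to treat the event. Report the number tested per arm beside each laboratory, urine and examination rate.

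The cost is one sentence and one reporting column. No visit is added; at the assumed rates, about 0.5 to 2 women per arm keep attending visits already planned. There are two limits: some women will decline further visits, and Visit 4 results after stopping may partly reflect treatment of the event.
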